### Data management and quality control of data

Both the case record form (CRF) and the web-based electronic database will be used to manage individual participant data. To protect confidentiality, the files are stored in a secure and locked place and manner, and the subject identification and private information will be deleted from all study documents. Quality control of the data will be handled at two different levels: the investigators will be required to ensure the accuracy of the data as the first level of control when they input the records in CRF. The second level will include data monitoring and validation that will be carried out by two full-time graduate students who will not be involved in the intervention or data collection. All the data will be double-inputted into the computer using Epidata3.0 software. After finishing the data entry and dealing with the query, the database will be locked under the orders of the principal investigator, and the SPSS software will be used for data analysis. No one is allowed to view the database without authorization; otherwise, they should notify the principal investigator.

### Statistical analysis

The Kolmogorov–Smirnov test will be used to test the normal distribution of continuous variables. Continuous variables will be presented by mean ± standard deviation (SD) if they are normally distributed or by median with interquartile range if they are not normally distributed. For the comparison of measurement data between the two groups, a *t*-test of two independent samples will be used for normal distribution data, and the Mann–Whitney *U* rank sum test will be used for non-normal distribution data. The comparison of count data between the two groups will be performed by *χ*^2^ test or Fisher’s exact test. An independent statistics expert will perform statistical analysis in a blind manner. SPSS for windows version 25.0 (SPSS Inc., Chicago, IL, USA) will be used for statistical analysis. The statistical level of significance will be set at *P* < 0.05.

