#### Withdrawal criteria

Participants who meet the criteria summarized below are withdrawn from the study. The subjects who are withdrawn after randomization will be followed up for outcomes. Reasons for withdrawal will be documented in follow-up records and data will be analyzed using the intention-to-treat (ITT) principle.

All subjects have the right to withdraw for any reasonThose who could not complete the test as required, with serious adverse events and complicationsFailed to have three consecutive telephone connections during the follow-up period at the end of the study

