### Outcome

The primary outcome indicators are healthy behaviors, readmission rate, and anxiety level, and the secondary outcome indicators are psychological capital, subjective well-being, and clinical indicators (including TC, LDL, HDL, blood glucose, body mass index, etc.).

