#### Primary outcome measure

Healthy behavior: The Health Promotion Lifestyle Profile II (HPLP II) will be used to measure patient’s healthy behavior. The scale was revised by American nursing scientist Walker [31], which mainly includes 6 dimensions and 52 items. The total Cronbach’s *α* coefficient of the scale is 0.94, and the Cronbach’s *α* number of each dimension is 0.79–0.87. Each item is scored by grades 1–4; the higher the score, the better the healthful lifestyle. It will be checked at visits 1, 8, and 9.Readmission rate: In this study, readmission is defined as the readmission caused by cardiovascular problems, including hypertension, angina, arrhythmia, cardiac insufficiency, etc., excluding the cases of readmission due to cold, tumor, and other factors. The readmission will be followed up by telephone for 3 months. The readmission information will be collected at visits 8 and 9.Anxiety: The Self-rating Anxiety Scale (SAS) will be used to measure the anxiety of patients with CHD. The scale was compiled by Chinese professor Zung (1971), there are 20 items on the scale, each item is scored by grades 1–4, and items 5, 9, 13, 17, and 19 are scored in reverse. According to the results of Chinese norm model results [32], the cut-off value of the SAS standard score is 50, of which 50–59 is mild anxiety, 60–69 is moderate anxiety, and over 69 is severe anxiety. The scale has been widely used in China and its validity and reliability have been verified (Cronbach’s *α* 0.82). The anxiety score will be measured at visits 1, 8, and 9.

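### The test for continuous outcomes is chosen by a normality pre-test and makes no stated use of the baseline scores; this costs precision and leaves the choice between means and ranks to the data, though the comparison stays valid

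*Protocol article*

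**What the plan says.** All from the protocol article.

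- Statistical analysis sets the pre-test: "The Kolmogorov–Smirnov test will be used to test the normal distribution of continuous variables". Normal data go to a *t*-"test of two independent samples will be used for normal distribution data"; otherwise the Mann–Whitney *U* "rank sum test will be used for non-normal distribution data". No covariate, change score, analysis of covariance or repeated-measures model is named.
- Outcome: "The primary outcome indicators are healthy behaviors, readmission rate, and anxiety level". Two of these three are continuous: healthy behaviours (HPLP II) and anxiety (SAS). Readmission is a proportion and is outside this point.
- Primary outcome measure, on HPLP II: "It will be checked at visits 1, 8, and 9". On SAS: "The anxiety score will be measured at visits 1, 8, and 9". Psychological capital, well-being and the clinical indicators follow the same three visits (Secondary outcome measure). The Baseline assessment section makes visit 1 the baseline; Table 1 puts visits 8 and 9 at weeks 12 and 24.
- Sample size calculation compares two independent means with SD 12.68 and difference 10.39, two-sided α 0.05 and power 0.8. It gives 25 per group, then 80 in total after 20% loss and other factors. It does not name the outcome behind the SD and difference.

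**The concern.** Two features of the stated method work against the trial.

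First, a baseline score usually predicts part of the follow-up score. A comparison that leaves it out keeps that predictable variation in the error term, so the interval is wider than the collected data require. With about 40 patients per arm, chance baseline differences are not negligible.

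Second, a *t*-test compares means, while a Mann–Whitney test compares ranks. If a pre-test on the trial's own data picks between them, the quantity to be reported is not fixed in advance. The sample size is framed only as a mean difference, so the planned effect may not be the one reported, and one outcome could be summarised differently at weeks 12 and 24.

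At stake are the width of the intervals for the continuous outcomes and a treatment effect defined before the data are seen.

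**Working it through.** **Inputs.** From Sample size calculation: σ = 12.68, δ = 10.39, Z = 1.96 and 0.842, 20% loss. From Study design and setting: 40 per arm, so 40 × 0.8 = 32 completers per arm. Assumed, because the documents are silent: baseline-to-follow-up correlation r = 0.3 to 0.7, and that σ and δ serve as a yardstick for a continuous primary outcome.

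**The plan's own figure.** 2[(1.96 + 0.842) × 12.68 / 10.39]² = 2 × 3.4196² = 23.39. Adding Z²/4 = 0.96 gives 24.35, so 25. The exact *t*-test solution is 24.38, also 25. (The formula as printed adds Z² = 3.84 and gives 27.23, so 28; that is a separate matter.) The stated 25 therefore reproduces for an unadjusted comparison of two means: the design, like the analysis, contains no baseline term.

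**Gain from baseline adjustment.** The residual SD becomes σ√(1 − r²) and the standard error of the difference is that SD × √(2/32). The half-width is 1.96 × SE. Power is from the noncentral *t* distribution with noncentrality δ/SE, two-sided α 0.05.

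| | Variance cut (r²) | Residual SD | SE | 95% CI half-width | Power at 10.39 |
|---|---|---|---|---|---|
| Unadjusted | 0% | 12.68 | 3.17 | 6.21 | 89.7% |
| r = 0.3 | 9% | 12.10 | 3.02 | 5.93 | 92.3% |
| r = 0.5 | 25% | 10.98 | 2.75 | 5.38 | 96.1% |
| r = 0.7 | 49% | 9.06 | 2.26 | 4.44 | 99.5% |

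In effective sample size, 32 per arm acts like 32/0.91 = 35, 32/0.75 = 43 or 32/0.51 = 63.

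**Chance baseline imbalance.** With 32 per arm, the SE of a baseline difference is 12.68 × √(2/32) = 3.17 points. Only a fraction r of it is expected to carry into follow-up: 0.95 / 1.6 / 2.2 points at r = 0.3 / 0.5 / 0.7. That variation is already inside the unadjusted SE; it is the part that adjustment removes.

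**Behaviour of the pre-test.** The rule was simulated with no treatment effect, 4,000 runs per setting and 32 or 40 per arm. A Kolmogorov–Smirnov test (Lilliefors form) was applied in each arm, with a switch to Mann–Whitney if either arm rejected at 0.05.

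| True distribution | Switched to Mann–Whitney (n = 32 / 40) | Type I error (n = 32 / 40) |
|---|---|---|
| Normal | 9% / 10% | 4.9% / 4.9% |
| Gamma, skewness 1 | 46% / 56% | 5.5% / 4.5% |
| Lognormal, log-SD 0.5 | 77% / 85% | 5.5% / 5.3% |

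Under moderate skew, whether means or ranks are compared is close to a coin toss, and even truly normal data switch about one time in ten. The error rate stays near 5%.

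**The case against.** The strongest reply is that nothing here is invalid. Randomisation keeps the unadjusted comparison unbiased, and at the plan's own difference it already has about 90% power with 32 per arm and 95% with 40, against a target of 80%. That stands: the gain is narrower intervals and better power for smaller effects, not rescue of an undersized trial.

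The size of the gain rests on r. Patients are recruited in hospital and assessed 12 and 24 weeks later, so a low r cannot be excluded, and at 0.3 the gain is modest. That stands too, and is why the range starts there.

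The article also does not say whether final values or changes from baseline are compared. A *t*-test on changes would use the baseline. But with equal SDs a change score has variance factor 2(1 − r), that is 1.4 / 1.0 / 0.6 at r = 0.3 / 0.5 / 0.7, against 0.91 / 0.75 / 0.51 for covariate adjustment. It is less efficient at every r shown and no better than final values at or below 0.5. The fair statement is that no use of baseline is stated.

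Three stronger readings are tempting, and the documents do not support them:

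- A reader might infer that the pre-test inflates the false-positive rate. The simulation shows 4.5–5.5%.
- A reader might infer that the whole chance baseline difference ends up in the estimate. Only r times it is expected to.
- A reader might infer that patients missing a visit will be dropped, against the promise that "data will be analyzed using the intention-to-treat (ITT) principle". The article sets out neither separate tests per visit nor a missing-data rule. That detail commonly sits in a fuller document not shown here, and Withdrawal criteria says withdrawn patients are still followed for outcomes.

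An unseen analysis plan does not remove the point itself, because the article states this method outright.

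**Conclusion.** The point holds as one of efficiency and prespecification. The stated method leaves collected baseline information without a role and lets the sample choose between a comparison of means and one of ranks. Over the assumed r = 0.3 to 0.7, adjustment removes 9% to 49% of residual variance. With 32 completers per arm it narrows the 95% CI half-width from about 6.2 to between 5.9 and 4.4 points, and lifts power at 10.39 from 90% to between 92% and 99%. The points scale rests on an SD that the protocol ties to no named outcome; the percentage cuts in variance do not depend on it. This is not a finding of bias, of inflated type I error or of inadequate power at the planned difference.

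**What to change.** For each continuous outcome, prespecify a linear model adjusted for the visit-1 score. Either of two forms will do: analysis of covariance at each of visits 8 and 9, or one mixed model with group, visit, group-by-visit and the visit-1 score. The first captures the precision gain quantified here; the second handles both visits in one fit. Report the adjusted mean difference with its 95% CI at each visit. Drop the Kolmogorov–Smirnov test as the rule for choosing the analysis, and keep a rank-based or bootstrap analysis only as a named sensitivity analysis.

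The cost is wording. The data are already scheduled and both models run in the planned SPSS 25. The Trial status section reports 20 volunteers recruited so far, so on the article's account the change can be made before the outcome data are analysed.

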#### Auditing

This study will be an interim trial review, independent of the investigator and sponsor.

#### Protocol amendments

Any possible amendments to the protocol during the course of the trial, including changes in study objectives, sample size, or study procedures, will require formal modifications to the protocol. The modification will be agreed by the project research team, approved by the Ethics Committee of Soochow University School of Medicine prior to implementation, notified to the Chinese government’s Ministry of Science and Technology, and reported to the participants as necessary.

## Discussion

At present, CHD has become the main cause of death of urban and rural residents in China [3] and is also one of the main reasons for the economic burden of chronic non-communicable diseases [2]. Its occurrence and development are closely related to unhealthy behaviors such as unreasonable diet, smoking, drinking, and so on [36]. Only relying on drugs or surgical treatment will not change the pathological progress of coronary atherosclerosis. Studies have shown that the higher incidence of ISR and MACE is associated with unhealthy behaviors [6, 7]. Therefore, it is of profound significance to change the unhealthy behaviors of patients to reduce the occurrence of cardiovascular events.

The American College of Cardiology (ACC) and the American Heart Association (AHA) issued the “2019 cardiovascular primary prevention guidelines,” which pointed out that adhering to a healthy lifestyle is an important measure to prevent cardiovascular disease [37]. Among the 15 special activities of healthy China, measures to promote a healthy lifestyle, such as reasonable diet, tobacco control, and national exercise, have been put in a prominent position. These above show the importance of healthy behaviors to the organism. Therefore, it is necessary to help patients establish healthy behaviors.

According to the “extension-construction” theory proposed by Fredrickson et al. [38], this theory believes that positive emotions can expand the thinking and action ability, and then build a series of enduring resources of individuals, so as to promote health and development. This study is based on the positive psychology of the experimental design, paying more attention to the potential positive forces of patients, helping patients to tap their own good quality, improve positive emotions, and promote positive development. Many experimental studies have confirmed that positive psychological intervention can help patients to improve anxiety, depression, and other bad psychology; improve their quality of life; improve treatment compliance; and help people quit smoking [16–18]. This study applies positive psychological intervention to patients after PCI for the first time, through systematic practice and training, to determine whether positive event records based on positive psychology will promote the establishment or maintenance of healthy behaviors, reduce the rate of readmission, improve negative emotions such as anxiety and depression, improve subjective well-being, etc., which will provide new ideas and references for the formulation of secondary prevention strategies for CHD.

Our trial has several advantages. Firstly, the purpose of our study is to explore the effects of positive event recording on healthy behaviors, readmission rate, and negative emotions such as anxiety and depression. At home and abroad, there have been studies on the clinical application of writing positive events, and our research team has previously conducted cross-sectional surveys of patient’s healthy behaviors, readmission status, and negative emotions such as anxiety and depression after PCI, which has a solid practical and theoretical foundation. Secondly, the intervention measure of this study is to record positive events by patients themselves, which can mobilize the enthusiasm of patients to actively participate in disease management. Thirdly, positive events recording discussed in this study belong to the secondary preventive measures for patients with CHD, which is also in line with the “two heart” nursing mode advocated by China now. This form of nursing intervention research is rarely reported in the field of CHD in China.

Despite the advantages of its results, our study has the following limitations. First of all, due to limited time, manpower, and funding, this study is only conducted in a hospital in Suzhou. In future trials, more patients with PCI in different levels of hospitals should be included to explore the role of positive psychology. Secondly, only one positive psychological intervention therapy is used in this study. In the future, a variety of progressive positive psychological intervention methods can be combined to test to determine a better treatment plan.

After the completion of this study, we will conduct large-sample, multi-center, and high-quality RCTs in future studies to further verify the role of positive event recording in the maintenance and promotion of health and provide a reliable evidence-based basis for the clinical promotion and application of positive event recording.

## Trial status

The study was registered with the Chinese Clinical Trial Registry (registration number: ChiCTR2000034538) on 10 July 2020. This study started to recruit volunteers on 11 July 2020 and is expected to complete the recruitment by 31 June 2021. So far, 20 volunteers have been recruited for this trial.

## Data Availability

The results of the trial will be disseminated through scientific journals or presentations at scientific conferences. This dataset is available from the corresponding author upon reasonable request.

## Abbreviations

ACC: American College of Cardiology
AE: Adverse event
AHA: American Heart Association
AIDS: Acquired immune deficiency syndrome
BMI: Body mass index
BP: Blood pressure
CHD: Coronary heart disease
CRF: Case record form
GWB: General Well-Being Scale
HDL: High-density lipoprotein
HIV: Human immunodeficiency virus
HPLP: Health Promotion Lifestyle Profile
ISR: In-stent restenosis
ITT: Intention-to-treat
LDL: Low-density lipoprotein
MACE: Major adverse cardiovascular events
PCI: Percutaneous coronary intervention
PPQ: Positive Psychological Capital Questionnaire
RCT: Randomized controlled trial
SAS: Self-rating Anxiety Scale
SD: Standard deviation
TC: Total cholesterol
TG: Triglyceride
